### Sample size calculation

The sample size was determined by utilizing the HAMD-17 scale score as the evaluative index. Based on previous study [33], after 8 weeks of treatment, the HAMD-17 score difference between the baseline and the endpoint in the acupuncture group should be approximately 10.79 ± 1.40, while the sham acupuncture group should be approximately 9.82 ± 1.80. Type 1 error is assumed at 0.05, and type 2 error is assumed at 0.2. PASS11.0 software (NCSS Statistical Software, Kaysville, UT, USA) has been used to determine the sample size, and the minimum sample size is 45 subjects for each group. Considering a dropout rate of 15%, a total of 106 subjects will be required with 1:1 allocation to each group (53 participants per group) for this study.

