Data management will be performed using Epidata software (v3.1, Odense, Denmark), with subsequent analyses conducted in IBM SPSS Statistics 25.0 (IBM Corp, Version 25.0, New York, USA). Baseline characteristics will be analyzed using FAS, while efficacy outcomes will be evaluated through both FAS and PPS. Safety assessments for acupuncture (Jin’s three-needle) intervention will be utilized SS. Continuous data will be statistically described using mean ± standard deviation and qualitative data will be provided as percentages or proportions, along with confidence intervals of 95%. Outcomes with multiple time points will be analyzed using repeated-measures analysis of variance (ANOVA), with treatment group and follow-up time as fixed effects and individual as a random effect, to compare the effect sizes at each time point. We plan to use the Shapiro – Wilk test to assess the normality of the residuals in the repeated measures ANOVA model. If the normality assumption is violated, we will consider appropriate non – parametric alternatives, such as the generalized estimating equations (GEE) approach. For between-group comparisons, normally distributed data with homogeneous variances will be analyzed using the two independent samples t-test. Non-normally distributed continuous variables or those with heterogeneous variances will be analyzed using the Kruskal-Wallis H test. All Statistical tests will be based on two-sided tests, with a significance level of α = 0.05 for statistically significant results. The Bonferroni test will be used for post hoc pairwise comparisons. We plan to conduct a sensitivity analysis to assess the impact of varying the assumed value of the Minimal Clinically Important Difference (MCID) (within a reasonable range based on existing literature and expert opinion) on the study findings and conclusions.

We will investigate whether acupuncture (Jin’s Three-Needle) regulates aberrant gene expression and DNA methylation patterns in the peripheral blood leukocytes of patients with mild-to-moderate depression. Details on molecular analysis are provided in S4 of the Supplementary File in S1 File.

The final statistical analyses will be conducted by an independent data analyst who is blinded to the treatment group allocation.

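### The rule that sends non-normal or unequal-variance comparisons to Kruskal-Wallis does not remedy unequal variances and leaves the mean-change hypothesis the trial is sized on, although the sample size itself assumes unequal SDs

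*Protocol article*

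**What the plan says.** The Outcomes section makes the primary outcome the HAMD-17 change from baseline to week 8. The Sample size calculation takes that change in the acupuncture group as "approximately 10.79 ± 1.40, while the sham acupuncture group should be approximately 9.82 ± 1.80", with "Type 1 error is assumed at 0.05, and type 2 error is assumed at 0.2", and concludes that "the minimum sample size is 45 subjects for each group". This is a comparison of two means with unequal SDs.

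The Statistical analysis section then gives two routes that can both reach HAMD-17:

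- **Repeated measures.** Outcomes with several time points go to a repeated-measures ANOVA with group and time as fixed effects and individual as a random effect. Residuals are checked with Shapiro-Wilk. If they fail, a non-parametric alternative is to be considered, "such as the generalized estimating equations (GEE) approach".
- **Between-group comparisons.** A t-test is used if the data are normal with equal variances. Otherwise: "Non-normally distributed continuous variables or those with heterogeneous variances will be analyzed using the Kruskal-Wallis H test".

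The Abstract places HAMD-17 at baseline and weeks 4, 6 and 8. The text does not say which route gives the primary week-8 result. Shapiro-Wilk is named only for the ANOVA residuals, and no test of equal variances is named.

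**The concern.** The second route lets the trial's own data choose the test, and its fallback does not suit one of its two triggers. With two arms, Kruskal-Wallis is the rank-sum test. It can be read as a test of location only if the two distributions have the same shape and spread, so unequal spread is a reason not to use it. The usual remedy, a t-test that allows unequal variances, is not mentioned.

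The switch also changes the question. The t-test branch compares mean changes, as the sample size does. The rank branch asks whether a JTN patient's change tends to exceed a sham patient's. It supplies no mean difference or confidence interval of its own, and no estimate with a standard error for the usual pooling over the planned multiple imputations. The planning SDs already fall in the unequal-variance branch, so this is a foreseeable outcome under the plan's own assumptions.

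Separately, GEE is called non-parametric. It is a regression model for means. It relaxes the normality assumption but is not a rank method.

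**Working it through.** **1. Inputs (Sample size calculation, Statistical analysis).** Mean changes 10.79 and 9.82, difference 0.97. SDs 1.40 and 1.80. Type I error 0.05, two-sided; power 80%. 45 per arm, or 53 with 15% dropout.

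**2. The plan's own figure.** Average variance = (1.40² + 1.80²)/2 = (1.96 + 3.24)/2 = 2.60, so SD = 1.612. Normal formula: n = 2 × 2.60 × (1.960 + 0.842)² / 0.97² = 43.4, rounded up to 44. The noncentral t gives about 79.6% power at 44 and 80.5% at 45, so 45 is reproduced. Dropout: 45/0.85 = 52.9, so 53 per arm and 106 in total, as stated.

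**3. How often a variance test would fire.** Variance ratio = 3.24/1.96 = 1.65. For the F-test, let c be its upper 2.5% point with n−1 and n−1 degrees of freedom. The chance of rejection is P(F > c/1.65) + P(F < 1/(1.65c)). The choice of variance test is an assumption.

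| Variance test | 45 per arm | 53 per arm |
|---|---|---|
| F-test (analytic) | 38% | 43% |
| Levene, continuous normal data (simulated) | 33% | 39% |
| Levene, whole-point scores (simulated) | 31% | 37% |

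**4. Adding a normality test.** HAMD-17 sums whole-point items, so changes are integers, and SDs of 1.4 to 1.8 leave few distinct values. The table shows simulated normal changes with Levene or Shapiro-Wilk on pooled residuals at 5%. Applying Shapiro-Wilk to this branch is an assumption.

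| Setting | Either fires, 45 per arm | Either fires, 53 per arm |
|---|---|---|
| SDs 1.40/1.80, continuous | 37% | 42% |
| SDs 1.40/1.80, whole points | 71% | 80% |
| SDs 2.8/3.6, whole points | 41% | 46% |
| SDs 4.2/5.4, whole points | 39% | 44% |

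Testing normality in each arm separately raises the whole-point figures to 91% and 97% at the planning SDs, and to 43% to 52% at the larger SDs.

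**5. The hypothesis after the switch.** With normal data at the planning values, the rank test addresses P(JTN change > sham change) = Φ(0.97/√(1.96 + 3.24)) = Φ(0.425) = 0.665, not the mean difference of 0.97.

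**6. Power with continuous normal data at the planning values.**

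| Procedure | 45 per arm | 53 per arm |
|---|---|---|
| Welch, no pre-test | 80.5% | 86.6% |
| Kruskal-Wallis | 78.5% | 85.1% |
| Switching (Levene or per-arm Shapiro-Wilk) | 79.4% | 85.8% |

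**7. Type I error with equal means and SDs 1.40/1.80.** The shapes are assumptions.

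| Shape | Kruskal-Wallis | Welch |
|---|---|---|
| Normal, both arms | about 5% | about 5% |
| Gamma with shape 2 (skewness 1.41), both arms | about 8% to 9% | about 5% |
| Exponential (skewness 2), both arms | about 13% to 16% | about 5% |
| Normal JTN, gamma-shape-2 sham | 11% to 12% | about 5% |

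With milder skew (skewness 0.5 to 1.0), Kruskal-Wallis rejects in 5.1% to 6.8%.

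**The case against.** The strongest reply is that Kruskal-Wallis may never touch the primary result. HAMD-17 has several post-baseline visits and so falls under the repeated-measures ANOVA. There a failed Shapiro-Wilk test leads to GEE, which still compares means. The t-test and Kruskal-Wallis sentence could be meant for baseline variables or single-visit comparisons. This stands as far as it goes: a reader might infer that Kruskal-Wallis decides the trial, and the text does not say so. Nor does it rule it out, since a week-8 change is also a between-group comparison.

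Three other strong readings are not supported:

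- **That the unequal SDs alone make the switch likely.** They give roughly one chance in three to two in five. The higher figures need a normality test in this branch and SDs as small as those planned.
- **That the plan's own assumptions inflate the error rate.** With normal data the rate stays near 5%, and with mild skew it rises little. The documents give no reason to expect the marked skew behind the larger figures.
- **That the rank test ignores baseline.** The outcome is a change from baseline, so this is wrong.

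It can also be said that detailed model specification belongs in an analysis plan not shown here. That is fair for covariates and covariance structure. It does not excuse a rule the article states outright and that does not suit its stated trigger.

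**Conclusion.** The point holds in this limited form. The Kruskal-Wallis rule is a poor choice for unequal variances and departs from the mean change used to size the trial, while the planning SDs are themselves unequal. The main harm is a data-dependent choice of test and a changed hypothesis. Loss of power is minor, and excess type I error arises only under skew that has to be assumed.

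If this route is applied to the week-8 change, the chance of switching is about 30% to 43% on a variance test alone. With a pooled normality test on whole-point scores it is about 70% to 80%, or about 40% to 50% if the true SDs are two to three times the planned ones. All these figures assume tests the plan does not name for this branch. Whether the route governs the primary result is left open by the text. Calling GEE non-parametric is a plain mislabel.

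**What to change.** - Remove the data-driven switch to Kruskal-Wallis.
- Name one mean-based primary analysis in advance: the week-8 contrast in HAMD-17 change from the planned repeated-measures model, with standard errors that allow unequal variances. State that this contrast is the primary result.
- Use Welch's t-test for any simple two-group comparison, without pre-tests.
- Keep the rank test as a sensitivity analysis only.
- Describe GEE, if retained, as a model for means and not as a non-parametric method.

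The cost is analysis wording only. The sample size stands, with Welch power of about 80% at 45 per arm and 87% at 53. As recruitment is under way, the change should be dated and recorded before the allocation is unblinded.

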### Statistical analysis

Intention-to-treat (ITT) will be used for the complete follow-up analysis. All randomized participants who received at least one treatment session and for whom at least one post-baseline assessment will be included for the full analysis in the full analytic dataset (FAS). Missing data will be replaced according to the principle of multiple imputations. Participants demonstrating strict protocol adherence and completing the full treatment course will be included in the Per Protocol Set (PPS) for efficacy analysis. All randomized participants who received at least one treatment will be included in the Safety Analysis Set (SS).

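### The only analysis named as a sensitivity analysis varies an MCID that is stated nowhere and enters no calculation, and it leaves the week-8 imputation untested

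*Protocol article*

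**What the plan says.** All references are to the Protocol article.

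- **Sensitivity analysis** (Statistical analysis). The plan is to assess how the findings and conclusions respond to "varying the assumed value of the Minimal Clinically Important Difference (MCID"), over a range to be drawn from published work and specialist judgement. The MCID is mentioned nowhere else, and no value is given.
- **Sample size** (Sample size calculation). The target difference is taken from earlier data: "Based on previous study [33], after 8 weeks of treatment", the mean HAMD-17 change "in the acupuncture group should be approximately 10.79 ± 1.40", "while the sham acupuncture group should be approximately 9.82 ± 1.80". It is not called an MCID.
- **Tests** (Statistical analysis). Repeated-measures ANOVA, with GEE as fallback, and a t-test or Kruskal-Wallis test between groups. "All Statistical tests will be based on two-sided tests, with a significance level of α = 0.05 for statistically significant results".
- **Missing data** (Statistical analysis). "Missing data will be replaced according to the principle of multiple imputations". The full analysis set needs at least one treatment session and one post-baseline assessment. The per-protocol set needs strict adherence and the full treatment course.
- **Withdrawal** (Safety). A participant whose depression worsens significantly may be offered antidepressants. Starting them counts as a major deviation and leads to withdrawal, with follow-up continuing for the safety analyses.

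**The concern.** A sensitivity analysis changes an assumption behind the primary result and shows how far the result moves. The assumption varied here is not behind the primary result. No described sample-size step, test, responder definition or decision rule uses an MCID, so whatever range is chosen, the estimate and its uncertainty stay where they were. The exercise can only change whether a fixed estimate is described as clinically relevant, and even there the article gives no starting value to vary from.

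Meanwhile an assumption that does feed the result goes untested by the analysis that carries the name. The withdrawal rule can make week-8 efficacy scores missing because the participant did badly. Standard multiple imputation takes the missing scores to be predictable from the observed ones. If those who leave do worse than their observed scores suggest, the imputed values are too favourable. A reader told that a sensitivity analysis was done may credit the result with a robustness check that does not bear on it.

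**Working it through.** **1. Does the sample size need an MCID?**

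Inputs, from Sample size calculation: means 10.79 and 9.82, SDs 1.40 and 1.80, and "Type 1 error is assumed at 0.05, and type 2 error is assumed at 0.2". Two-sided testing comes from Statistical analysis.

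- Difference: 10.79 − 9.82 = 0.97 points.
- Common SD: √((1.40² + 1.80²)/2) = √2.60 = 1.612. Standardised difference: 0.97/1.612 = 0.60.
- Normal approximation: n = 2 × (1.960 + 0.842)² × 2.60/0.97² = 43.4, so 44 per group.
- Noncentral t: power is 0.797 at 44 and 0.806 at 45, so 45 per group. This matches the article: "the minimum sample size is 45 subjects for each group".
- Dropout: 45/0.85 = 52.9, so 53 per group and 106 in total, as stated.

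The figures reproduce in full with no MCID among the inputs. The sample-size arithmetic is correct and is not part of this point.

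**2. Does any described analysis use an MCID?**

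| Element | Depends on an MCID? |
|---|---|
| Sample size | No (step 1) |
| Repeated-measures ANOVA or GEE | No, null is zero difference |
| t-test or Kruskal-Wallis test | No, null is no difference |
| Responder definition, margin or decision rule | None described |
| Wording on clinical relevance | Could, but no value or criterion is given |

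**3. What does the named analysis leave untested?**

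The missing-data rule and the withdrawal rule, read together, mean that a participant who worsens and starts antidepressants may have no week-8 HAMD-17 for efficacy. The article mentions continued follow-up for safety only. If such a participant has an earlier post-baseline score, the week-8 value is imputed. The per-protocol set drops the participant, so it does not vary the imputation assumption.

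Illustration of size. The bias is an assumption, shown as a range. The share is capped at the planned 15% dropout and applied to the JTN arm only.

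Shift in the difference = share × bias.

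- Bias 0.5: 0.15 × 0.5 = 0.075, about 0.08 points; 0.075/0.97 = 8%.
- Bias 2: 0.15 × 2 = 0.30 points; 0.30/0.97 = 31%.

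**4. Why significance should not stand in for relevance**

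Smallest significant difference = t × SD × √(2/n), by a two-sample t approximation with the article's SDs:

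- n = 45: 1.987 × 1.612 × √(2/45) = 0.68 points.
- n = 53: 1.983 × 1.612 × √(2/53) = 0.62 points.

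These depend on the SD. The threshold reaches one point at a common SD of 2.39 (45 per group) or 2.60 (53 per group). At SD 3 it is 1.26 or 1.16.

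**The case against.** The strongest reply has four parts.

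- **Scope.** This is a condensed article, and imputation details and tipping-point analyses commonly sit in a statistical analysis plan that is not shown. This stands in part: a missing tipping-point analysis would not be a finding by itself. The article does, however, commit to a specific analysis as its sensitivity analysis, and that analysis cannot do the job. The remedy replaces something stated.
- **The MCID exercise is not empty.** Reading one estimate and interval against several thresholds can change a conclusion about relevance, and the article does speak of conclusions. This stands. A reader might infer a check that can never fail; the text supports only that it cannot alter the estimate, interval or p value.
- **It is not the only second look.** Efficacy is also analysed in the per-protocol set. This stands, so the claim is limited to the only analysis carrying the name. The per-protocol analysis still does not test the imputation.
- **The magnitudes are soft.** The bias is assumed. The 15% is a dropout allowance, and the full analysis set leaves out anyone with no post-baseline assessment, so the imputed share may be smaller. Similar bias in both arms would largely cancel. Even the largest shift takes 0.97 to 0.67, roughly at the 0.62 to 0.68 threshold, so no reversal is shown. All of this stands, and the range is illustrative only.

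**Conclusion.** The concern holds in this limited form. The one analysis named as a sensitivity analysis varies a quantity that the article neither states nor uses. It cannot test the robustness of the primary result, and it leaves the week-8 imputation assumption unexamined. The first part rests on the text and on the reproduction of 45 and 106 without an MCID. The second rests on reading the withdrawal and missing-data rules together. Its size, about 0.08 to 0.30 points or 8% to 31% of 0.97, is conditional on a bias of 0.5 to 2 points in at most 15% of the JTN arm.

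Three stronger readings are tempting and not supported:

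- That the plan declares success at p < 0.05. It sets a significance level, not a rule for claiming efficacy.
- That significance below one point is itself a defect. It depends on SDs of 1.40 and 1.80, and in any trial with 80% power significance can be reached below the target difference. It shows only that significance should not be presented as clinical relevance.
- That the Discussion promises a clinically relevant effect. Its closing sentence speaks of clinically relevant evidence to guide later, larger trials.

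**What to change.** Before unblinding:

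1. Replace the MCID variation, as the sensitivity analysis, with a delta-adjusted (tipping-point) version of the planned multiple imputation for week-8 HAMD-17. Imputed JTN scores are worsened in prespecified steps, and the estimate, 95% CI and p value are reported at each step, with the step at which the conclusion changes.
2. If an MCID is kept, fix one value for the between-group week-8 difference, with its source, and read the estimate and 95% CI against it. Label this as interpretation. The value is for the investigators to choose and justify.
3. State that statistical significance alone will not be described as clinical relevance.

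The cost is a change of wording and one extra analysis on data already being collected; the sample size does not change. The downside is that the statement on robustness or relevance may turn out less favourable.

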## Discussion

JTN treatment for patients with mild-to-moderate depression has not been thoroughly investigated. This randomized controlled trial aims to (1) evaluate the efficacy and safety of JTN treatment for mild-to-moderate depression and (2) examine the underlying mechanisms of its therapeutic effects in treating depression.

Individuals with mild-to-moderate depression typically exhibit fewer and less severe depressive symptoms. Often, there are no observable signs of low mood or psychomotor retardation. However, mild-to-moderate depression can easily progress to major depressive disorder. Major depression significantly impacts patients’ physical health, social functioning, and daily activities, representing a condition with a high disease burden [34]. Therefore, it is crucial for clinicians and researchers to develop effective interventions to manage mild-to-moderate depression and prevent its progression to more severe forms.

Acupuncture is widely applied in clinical practices across China. The efficacy of acupuncture is primarily determined by the careful selection and strategic combination of acupuncture points and standardized procedures. In our study, the JTN treatment was thoroughly developed based on TCM theory and expert acupuncturists’ clinical experience, which has been practiced for decades. A key characteristic of JTN lies in its unique approach to acupoint selection. The JTN treatment protocol incorporates multiple acupoint groups, with each group comprising three to four specialized acupoints carefully selected according to local points, influential points, or empirical points. JTN demonstrates therapeutic efficacy in treating mental disorders and assisting patients in modulating their mental states. In China, acupuncture methods are widely utilized by practitioners to manage depression. Numerous clinical trials have shown that it might effectively alleviate patients’ symptoms, highlighting its therapeutic validity and clinical relevance [35]. Several studies have demonstrated that acupuncture may not only serve as a safe adjunctive treatment combined with antidepressants but also exhibit greater efficacy in alleviating depressive symptoms [36–38]. Unlike conventional acupuncture, JTN integrates local, influential, and empirical points to achieve layered therapeutic effects on somatic, emotional, and energetic levels. For instance, the combination of HT7 (Shenmen), ST36 (Zusanli), and GB20 (Fengchi) in JTN simultaneously targets serotonin regulation, immune modulation, and vagal nerve activation [39]. Lin, W., et al. suggest JTN may offer superior symptom relief and lower tolerance risks compared to standard acupuncture [40], positioning it as a promising intervention for preventing depression progression. As evidenced by previous studies, JTN has been widely employed to alleviate symptoms of depression and anxiety, as well as enhance sleep quality [41]. Although growing evidence indicated that acupuncture was a very promising treatment for depression, there was still insufficient evidence [42] to determine the efficacy of acupuncture due to lacking well-designed studies. Therefore, we will rigorously adhere to the SPIRIT statement and STRICTA recommendations, standardizing our study protocol to elucidate the underlying mechanisms of acupuncture (Jin’s Three-Needle) in treating mild-to-moderate depression.

Our study design incorporates safeguards to minimize potential biases. However, several limitations merit consideration. First, the single-center approach lacks regional diversity. Second, due to the lack of a planned post-intervention follow-up period, the long-term outcomes and durability of treatment effects could not be assessed. Third, depression diagnosis relies on subjective assessments without validated biomarkers, potentially introducing selection and measurement biases. Fourth, practitioner blinding was impossible given the intervention’s technical requirements, creating a risk of performance bias. We are currently working to standardize this trial’s procedure.

In conclusion, the results of this trial will provide evidence regarding the effectiveness and safety of JTN treatment for patients with mild-to-moderate depression and offer high-quality, clinically relevant evidence to inform the design of future larger-scale randomized controlled trials.

